#### Secondary outcomes

Evaluation of the following histological changes after 96 weeks of treatment according to NASH-CRN criteria:
Improvement of at least 1 point in the different components of the NASH-CRN score (steatosis, liver ballooning, and lobular inflammation)Resolution of fibrosisFibrosis improvement along with NASH improvement, defined as at least 1 stage improvement in fibrosis and at least 2 points less in NAFLD activity score (NAS) with at least 1 point of improvement in ballooning and lobular inflammation.Improvement in NASH score of at least 2 points with no worsening of fibrosis.

Evaluation of potential complications and morbimortality related to the procedures such as bleeding, bronchial aspiration, infections, suture dehiscence, and death.

Evaluation of the following secondary endpoints after 96 weeks of treatment:
Cardiovascular events: Ischemic heart disease, stroke, peripheral arterial disease, heart failure, and cardiomyopathy.Liver-related death.Liver profile changes and liver function biomarkers.Changes in non-invasive markers of fibrosis and steatosis.
Serological markers: NAFLD fibrosis score, FIB-4, and Hepamet score. Several predictive models of advanced fibrosis are based on formulas using clinical and analytical parameters.FibroScan and CAP: Transitional elastography or FibroScan is the most widespread technique in the non-invasive diagnosis of liver fibrosis. It measures by ultrasound the speed of propagation of low-frequency waves through the liver parenchyma. CAP is an application of FibroScan that measures the degree of attenuation of the ultrasound wave transmitted through the liver proportional to the amount of liver fat.DEMILI: Computerized optical analysis software of conventional liver magnetic resonance images that determines a number of optical biomarkers that allow the detection of NASH and the prediction of significant fibrosis.Metabolomic profile: Owl-liver. Serum analysis for the determination of fatty liver disease and NASH diagnosis based on the determination of more than 500 serum metabolites by liquid chromatography coupled to mass spectrometry. Using the method developed by the company OWL (ONE WAY LIVER, S.L., Derio -Vizcaya-).Changes in lipid parameters: Cholesterol, LDL, HDL, and triglyceridesVariation in body weight.Changes in endothelial dysfunction biomarkers: ICAM-1, VCAM-1, E-selectin, P-selectin, angiopoietin-2, endocan, RBP4, OPG, and ADMA.Changes in macrophage activation biomarkers: Gal 3, Gal-3BP, sCD163, and sCD14.Changes in the glucose homeostasis biomarkers and insulin resistance: glucose, hemoglobin A1c (HbA1c), homeostatic model assessment for insulin resistance (HOMA-IR), adiponectin, retinol-binding protein 4 (RBP-4), monocyte chemoattractant protein-1 (MCP-1), plasminogen activator inhibitor-1 (PAI-1), leptin, resistin, visfatin, and apelin.Changes in the intestinal microbiota by sequencing the 16S rRNA in stool samples.Changes in inflammation biomarkers: fibrinogen, hs-CRP, haptoglobin, TNF-alpha, IL-6, and IL-1β.Changes in serum expression of incretins: GLP-1, GIP, and YY peptide.Changes in the cardiovascular risk profile.
Study of classic risk factors: Framingham scale.Study of emerging vascular risk factors: hcPCR, homocysteine, and Lp(a)Lipid biomarkers: PON1 and PCSK9Qualitative alterations of lipoproteins.Evaluation of endothelial function by digital pulse plethysmography (ENDO-PAT2000 -Itamar Medical Inc., Caesarea, Israel-).Evaluation of the presence of subclinical atherosclerosis by carotid ultrasound.Changes in mineral metabolism parameters: Parathormone (PTH), 25-hydroxy-vitamin D (25OHD), N-terminal propeptide of collagen type I (PINP), and beta-cross laps (β-CTX).Changes in serum levels of gastrointestinal hormones: glucagon-like peptide-1 (GLP-1), glucose-dependent insulinotropic polypeptide (GIP), tyrosine thyrosine peptide (PYY), ghrelin, oxymodulin (OXM), cholecystokinin (CKK), and fibroblast growth factor 19 (FGF-19).Changes in the quality of life (36-item shortened health questionnaire [SF-36]), eating habits (Eating Habits Questionnaire), and physical activity (Global Physical Activity Questionnaire [GPAQ]) based on patients reported outcomesSafety and tolerability: number of adverse effects resulting from treatment during the study.Economic evaluation of both interventions with a cost-effectiveness analysis.

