### Objectives {7}

#### Hypotheses

In patients with non-alcoholic steatohepatitis (NASH) and obesity, ESG will achieve weight loss and improvement in metabolic comorbidities and liver histology equal to or greater than LSD with a lower rate of adverse effects.

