#### Participant timeline {13}

##### Participant timeline

**Table Tabb:** 

PROCEDURES	WEEK 2	WEEK 8	WEEK 12	WEEK 24	WEEK 48	WEEK 72	WEEK 96
**Liver biopsy**							**X**
**QL questionnaires**					**X**		**X**
**Cardiovascular events**							**X**
**Fecal samples**							**X**
**Blood analysis**		**X**	**X**	**X**	**X**	**X**	**X**
**Safety: SAE and RAE**	**X**	**X**	**X**	**X**	**X**	**X**	**X**
**Dietary recommendations**	**X**	**X**	**X**	**X**	**X**	**X**	**X**
**Fibrosis evaluation**							**X**
**Ultrasound proof**					**X**		**X**

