#### Assignment of interventions: blinding

Given the nature of this study where surgical procedures are performed versus an endoscopic procedure, the study staff cannot be blinded.

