#### Who will be blinded {17a}

Not applicable

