### Statistical methods

#### Statistical methods for primary and secondary outcomes {20a}

Data will be analyzed using SPSS version 19. A descriptive baseline and end-of-follow-up analysis (week 96) of the data will be performed using the mean and standard deviation or the median and range where appropriate for quantitative data and percentage for qualitative data. Quantitative variables will be compared with Student’s *t* test and qualitative variables will be compared with *X*^2^. When variables do not follow a normal distribution, non-parametric tests should be used. Paired data tests will be used to analyze baseline and 96-week results.

All changes in efficacy parameters endpoints will be analyzed in an intention-to-treat and per-protocol analysis and grouped by randomized treatment.

The Intent-to-Treat (ITT) population will include all subjects randomized to treatment. The per-protocol (PP) population will be a subset of the ITT population, excluding subjects that violate key protocol criteria, with the exact list of exclusion reasons to be included in the statistical analysis plan (SAP).

The primary efficacy endpoint, by histopathological improvement of fibrosis by at least 1 stage without any worsening of NASH, and histopathological resolution of NASH without any worsening of the stage of fibrosis will be conducted on the intention-to-treat (ITT) population; so all randomized subjects will be included in the primary analysis.

Secondary endpoints analyzed by descriptive statistics and inferential statistics will include ANOVA. Non-parametric tests may be utilized such as Wilcoxon rank-sum.

For all tests, we will use 2-sided *p* values with alpha < 0.05 level of significance.

All safety variables (i.e., adverse events, laboratory data, vital signs, and ECG) will be summarized by treatment for all patients of the safety set. Descriptive statistics using appropriate summary statistics will be calculated for quantitative safety data as well as for the difference to baseline, when appropriate. In addition, a shift table describing out-of-normal range shifts will be provided for clinical laboratory results.

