#### Adverse event reporting and harms {22}

The investigators will be responsible for collecting all the adverse events in the clinical history based on those referred by the patient spontaneously or by an interview in the follow-up visits. The causality of the adverse event with the intervention will be evaluated and recorded in the clinical history and in the CRF.

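### The hypothesis of fewer adverse effects with ESG rests on a count of events attributed to treatment in an open-label trial, and the plan leaves the status of the between-arm safety comparison unclear

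*Protocol article*

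**What the plan says.** **Claim.** The Hypotheses section expects ESG to do at least as well as surgery on weight, metabolic comorbidities and liver histology, "with a lower rate of adverse effects". The abstract's aim also covers a comparison of safety. No size of difference or margin is given.

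**Endpoints.** Under Secondary outcomes, safety and tolerability is defined as the "number of adverse effects resulting from treatment during the study". A separate item in the same section reads "Evaluation of potential complications and morbimortality related to the procedures such as bleeding, bronchial aspiration, infections, suture dehiscence, and death".

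**Collection and attribution.** Section {22} makes the investigators responsible for collecting all adverse events, from spontaneous report or interview. It then adds: "The causality of the adverse event with the intervention will be evaluated and recorded". The participant timeline labels its safety row "Safety: SAE and RAE", and the article does not define RAE.

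**Blinding.** The blinding section says that "the study staff cannot be blinded", and section {17a}, on who will be blinded, reads "Not applicable". No independent or blinded adjudication of events is mentioned, and no data monitoring committee is planned.

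**Analysis.** Section {20a} says the safety variables (adverse events, laboratory data, "vital signs, and ECG) will be summarized by treatment" for the safety set. The same section gives secondary endpoints both descriptive and inferential statistics, compares qualitative variables by chi-square, and sets a two-sided 0.05 level for all tests.

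**The concern.** Better safety is the advantage the hypothesis claims for ESG, so the endpoint behind it should be able to support a comparison. As worded it has three weaknesses.

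1. **Attribution.** Counting only events that result from treatment puts a judgement between the event and the endpoint. The article itself presents endoscopy as the less invasive option and stresses the complications of surgery. Expectations of that kind can influence causality judgements when the procedure is known.
2. **No patient denominator.** The hypothesis speaks of a rate, while the endpoint is a number of events. With 15 patients per arm, one patient with repeated events can move the total.
3. **Unclear comparison.** The sentence that names adverse events promises summaries by arm. The sentence on secondary endpoints promises inference. A reader cannot tell which one governs the safety claim.

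The risk is that a difference in raw attributed counts is reported as a lower rate, with no interval to show how little 15 per arm can establish.

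**Working it through.** **Is there a figure to reproduce?** Not for safety. The only sample-size figure is 30 (15 per arm), for NASH resolution. It reproduces from 85% versus 25% with unpooled variance, two-sided alpha 0.01 and power 0.90:

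n = (2.576 + 1.282)² × (0.85×0.15 + 0.25×0.75) / 0.60² = 14.88 × 0.315 / 0.36 = 13.02

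Rounded up to 14 and multiplied by 1.07 for the 7% loss, this is 14.98, so 15 per arm. Adverse events play no part in it.

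The rest is illustration. All event and attribution rates below are assumptions, because the article gives none.

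**1. Attribution.** Let both arms have the same true mean number of events per patient, m, and let a share a of events be attributed to treatment. The expected count is 15 × m × a, so the apparent rate ratio, ESG to LSG, is a(ESG)/a(LSG) whatever m is.

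| Attributed, LSG | Attributed, ESG | Expected counts at m = 1 | Apparent ratio |
|---|---|---|---|
| 60% | 60% | 9.0 vs 9.0 | 1.00 |
| 70% | 50% | 10.5 vs 7.5 | 0.71 |
| 80% | 40% | 12.0 vs 6.0 | 0.50 |

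The true ratio is 1 in every row. Attribution could also run the other way and put ESG at a disadvantage; the documents do not settle the direction.

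**2. Events versus patients.** Let five of 15 patients in each arm have an event. With one event each in the ESG arm, the count is 5. If one of the five LSG patients has k events and the other four have one each, the LSG count is 4 + k. At k = 6 that is 10, twice the ESG count, although the proportion of patients affected is 5/15 in both arms.

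**3. Precision per patient.** The Newcombe 95% interval combines the Wilson limits (l, u) of the two proportions:

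lower = d − √[(p₁−l₁)² + (u₂−p₂)²]; upper = d + √[(u₁−p₁)² + (p₂−l₂)²]

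- LSG 8/15 = 0.533, Wilson 0.301 to 0.752. ESG 3/15 = 0.200, Wilson 0.070 to 0.452.
- d (LSG − ESG) = 0.333.
- Lower: 0.333 − √(0.232² + 0.252²) = 0.333 − 0.343 = −0.009 (unrounded inputs).
- Upper: 0.333 + √(0.219² + 0.130²) = 0.333 + 0.254 = 0.587.

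So 8/15 versus 3/15 gives −1 to 59 points as LSG minus ESG, or −59 to +1 as ESG minus LSG. With 5/15 in each arm the interval is −31 to +31.

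**4. Power with 15 per arm, two-sided 0.05** (exact enumeration, share of patients with an event)

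| LSG vs ESG | Fisher exact test |
|---|---|
| 20% vs 5% | 0.08 |
| 30% vs 10% | 0.15 |
| 40% vs 10% | 0.33 |
| 50% vs 20% | 0.25 |
| 60% vs 20% | 0.45 |

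For 50% versus 20%, the uncorrected chi-square test has power 0.42.

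**5. Passages set side by side.** Section {22} collects every adverse event and records causality as a separate item, so an analysis regardless of cause needs no new data. The timeline row names SAE and RAE. If RAE means related adverse events, which is an inference, non-serious unrelated events would fall outside that row although section {22} includes them. In section {20a}, the safety sentence and the secondary-endpoint sentence give different treatments to an outcome that is both a safety variable and a secondary endpoint.

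**The case against.** **Safety is not clearly limited to description.** A reader of the safety sentence alone might infer that adverse events will only be described. The document does not support that: section {20a} also gives secondary endpoints inferential statistics, and safety is one of them. What stands is that the two statements need reconciling.

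**A test free of attribution is possible.** A reader might also infer that the safety claim cannot be tested without bias. That goes too far. All adverse events are collected, and the complications outcome names harder events such as bleeding, suture dehiscence and death. That outcome is still restricted to events related to the procedures, and its list is open-ended, so it only partly avoids the problem.

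**Who judges causality is not stated.** Section {22} names the investigators for collection only. That unblinded staff make the judgement is a fair inference from the lack of blinding. That the operators make it is not documented. The endpoint wording could also be a loose rendering of treatment-emergent, in which case attribution would not enter.

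**Some of this belongs in the analysis plan.** The counting unit and the interval method are often left to an SAP, and this article refers to one. Their absence is not the point. The point is that the article states an attributed count as the endpoint for a rate claim, and makes two statements about its analysis that do not agree.

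**The remedy has limits.** Events of any cause over 96 weeks may be common in both arms and dilute a procedural difference. Reporting by patients who know their procedure stays open to bias. Both objections are correct, and they are reasons to keep attributed events as supportive results.

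**Conclusion.** The concern holds in limited form. The stated safety and tolerability endpoint is a poor basis for claiming a lower adverse-effect rate: it counts events, on its natural reading it depends on attribution without blinding, and the plan is unclear on whether the arms are formally compared. A patient-level comparison regardless of cause is better and uses data already planned.

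The size of any distortion is unknown. Under equal true rates, the assumed attribution patterns give apparent ratios from 1.00 down to 0.50; these show what could happen and predict nothing. The firmer result is imprecision. With 15 per arm, even an observed 33-point difference (8/15 versus 3/15) has an interval that just includes zero, and Fisher power is 0.08 to 0.45 for assumed differences of 15 to 40 points. The conclusion assumes that resulting from treatment means judged to be caused by it, and that no blinded adjudication exists beyond what the article states.

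**What to change.** 1. For the safety claim in the hypothesis, compare the proportion of patients with at least one adverse event of any cause to week 96, and the proportion with at least one serious adverse event. Report each as ESG minus LSG with a score-based 95% interval, for example Newcombe.
2. Report the listed procedural complications in the same way, per patient.
3. Keep treatment-attributed events and event counts as supportive results, and say what resulting from treatment means and who judges causality.
4. Reconcile the two statements in section {20a}, so that it is clear whether the safety comparison is inferential or descriptive. Define RAE and align the timeline row with section {22}.
5. Claim a lower rate only if the ESG minus LSG interval lies wholly below zero. Otherwise present the result as an estimate.

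The cost is wording and one table from data already collected. The price is a wide interval that may not support the hypothesised advantage, possible dilution by unrelated events, and open-label reporting bias, which this change does not remove.

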#### Participant timeline {13}

##### Participant timeline

**Table Tabb:** 

PROCEDURES	WEEK 2	WEEK 8	WEEK 12	WEEK 24	WEEK 48	WEEK 72	WEEK 96
**Liver biopsy**							**X**
**QL questionnaires**					**X**		**X**
**Cardiovascular events**							**X**
**Fecal samples**							**X**
**Blood analysis**		**X**	**X**	**X**	**X**	**X**	**X**
**Safety: SAE and RAE**	**X**	**X**	**X**	**X**	**X**	**X**	**X**
**Dietary recommendations**	**X**	**X**	**X**	**X**	**X**	**X**	**X**
**Fibrosis evaluation**							**X**
**Ultrasound proof**					**X**		**X**

##### Sample size {14}

Previous studies have shown a resolution of NASH in the 85% of patients undergoing a bariatric surgery (69.6% in gastric tubing surgery) and a resolution of 25% in patients with a lifestyle intervention. A bilateral ratio comparison test was used for sample size calculation with a confidence level of 99%, a statistical power of 90%, and an assumption of 7% loss. Obtained sample to observe differences is *n*=30 (15 per treatment arm).

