On the other hand, physical activity comprised of aerobic to 1 year [14, 15] improves the hepatic histology of an independent way to the loss ponderal.

Bariatric surgery (BS) is a very effective treatment to induce the loss of weight in subjects with morbid obesity; in fact, surgical procedures are clearly superior to physical exercise and the diet in long-term weight control [16, 17]. Clinical evidences suggest that bariatric surgery in obese patients with NASH can improve all its histological components, including steatosis, inflammation, and fibrosis [18, 19]. Lassailly et al. [18] demonstrated that 1 year after surgery, resolution of NASH occurred in 85% of the patients.

The efficacy of the bariatric surgery on the NASH has been assessed in several previous studies [20–31]; however, these findings have been limited by the large heterogeneity observed in populations and size of the studies. A metaanalysis [32] carried out on 15 studies including 766 patients with hepatic pared biopsies, demonstrated that the steatosis was improved in 91.6% of the patients, the NASH in 81.3% of patients, and the fibrosis in 65.5% of the patients. The global result of these studies also demonstrated that the BS is capable of normalizing the hepatic biomarkers and of improving the histological alterations in patients with NASH, although in some isolated studies there has been observed a minimal progression of fibrosis [29–31].

Nevertheless, in spite of these benefits, a 2010 Cochrane revision suggested that the evidence was insufficient to evaluate the results of the surgery as an option of treatment in patients with NASH [33]. In the same way, a metaanalysis of 2015 suggests that improves the hepatic histology and diminishes hepatic biomarkers, but it also concludes major quality evidences must take place before coming to convincing conclusions on the benefits of the bariatric surgery for the NAFLD [34].

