### Outcomes {12}

#### Primary outcome

Assessment of the efficacy of endoscopic vertical gastroplasty + lifestyle modification against laparoscopic vertical gastrectomy + lifestyle modification in the histological improvement of NASH from baseline to week 96 by the following:
Improvement of fibrosis in at least 1 stage without worsening of NASH.Resolution of NASH without worsening of fibrosis.

The resolution of NASH is defined as the histopathological disappearance of ballooning and the disappearance or persistence of minimal lobular inflammation (grade 0 or 1) using the NASH CRN scoring system with a type of general lesion that does not qualify as steatohepatitis. Worsening of fibrosis is defined as the progression of at least one stage.

For all the patients, a basal liver biopsy should be obtained prior to the execution of the therapeutic technique and a subsequent biopsy 96 weeks after the procedure should also be obtained.

To avoid inter-observer variability, the histological evaluation will be assessed by two local pathologists independently.

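### The 90% power in the sample-size section was calculated for NASH resolution alone, not for resolution without fibrosis worsening at week 96

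*Protocol article*

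**What the plan says.** All references are to the protocol article.

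- **Sample size {14}** starts from "Previous studies have shown a resolution of NASH in the 85% of patients undergoing a bariatric surgery", adds "69.6% in gastric tubing surgery" for the sleeve-type operation, and sets against these "a resolution of 25% in patients with a lifestyle intervention". All three are rates of resolution. None carries a fibrosis condition or a time point. The calculation is two-sided at 99% confidence, with 90% power and 7% loss, and gives 30 patients, 15 per arm.
- **Introduction {6a}** cites a surgical study in which "1 year after surgery, resolution of NASH occurred in 85% of the patients". It also summarises a meta-analysis of bariatric surgery, and mentions minimal fibrosis progression in some isolated studies.
- **Objective {7}** and **Trial design {8}** aim at resolving NASH with no worsening of fibrosis.
- **Primary outcome {12}** is assessed "in the histological improvement of NASH from baseline to week 96" and has two listed components: improvement of fibrosis by at least one stage with no worsening of NASH, and "Resolution of NASH without worsening of fibrosis". Progression by one stage counts as worsening.
- **Statistical methods {20a}** repeats both components and sets two-sided alpha at 0.05.

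**The concern.** The event that sized the trial is not the event the trial counts. A patient whose NASH has resolved but whose fibrosis has risen by one stage is a success under the planning rates and a failure under the objective and the second primary component. The 85% also appears to be a one-year figure, while the trial reads its outcome at about two years.

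A reader of the sample-size section will take 90% as the chance of detecting the planned effect on the primary endpoint. If the stricter definition narrows the difference between arms, the real figure is lower, and the calculation has little room for that: it needs 13.02 per arm and has 14 after the assumed losses.

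**Working it through.** **Inputs.** 85%, 25%, two-sided 1%, 90% power, 7% loss and 15 per arm are from Sample size {14}. Two-sided 5% is from Statistical methods {20a}. The share w of resolved patients who fail the fibrosis condition is in neither section and is an assumption.

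**1. Reproducing the plan's figure.** With the unpooled normal approximation for two proportions,

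n per arm = (z₀.₉₉₅ + z₀.₉₀)² × [p₁(1−p₁) + p₂(1−p₂)] / (p₁−p₂)²

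= (2.576 + 1.282)² × (0.1275 + 0.1875) / 0.60² = 13.02, rounded up to 14.

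14 × 1.07 = 14.98, so 15 per arm and 30 in total. This matches. Using 69.6% against 25% in the same formula needs 30 per arm before losses, so the 69.6% did not produce N = 30. The 90% therefore belongs to 85% versus 25% for NASH resolution alone.

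**2. Comparing the events.** Resolution without fibrosis worsening is a subset of resolution. At one time point its rate is equal or lower, in each arm. How much lower is not documented.

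**3. Illustration with a common w.** Set p₁ = 0.85(1−w) and p₂ = 0.25(1−w), with 14 per arm:

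power = Φ( (p₁−p₂) / √{[p₁(1−p₁) + p₂(1−p₂)]/14} − z )

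with z = 2.576 at 1% and 1.960 at 5%. For w = 0 the ratio is 0.60/√(0.315/14) = 4.00, which gives Φ(1.424) = 92% at 1%.

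| w | p₁ | p₂ | n per arm for 90% at 1%, before loss | Power at 1% | Power at 5% | Exact chi-square power at 1% | at 5% |
|---|---|---|---|---|---|---|---|
| 0 | 85.0% | 25.0% | 13.0 | 92% | 98% | 82% | 92% |
| 5% | 80.8% | 23.8% | 15.4 | 86% | 96% | 76% | 88% |
| 10% | 76.5% | 22.5% | 18.1 | 79% | 92% | 69% | 83% |
| 15% | 72.3% | 21.3% | 21.0 | 72% | 88% | 62% | 79% |

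**4. How far the direction depends on the assumption.** At w = 2% the power at 1% is still 90.1%. If the loss is unequal, for example 85% to 80% and 25% to 15%, the difference widens to 65 points and power at 1% rises to 97.5%.

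**5. What the table does not describe.** The 25% is a lifestyle rate, and neither trial arm is lifestyle alone. For two active arms, again with 14 per arm and the unpooled formula, power at 5% is 17% for 85% versus 69.6% and 20% for 69.6% versus 49.6% (at 1%: 6% and 7%). These pairs are assumptions; the documents give no rate for ESG.

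**The case against.** The strongest reply is that power depends on the difference between arms, not on the level of the rates, so a stricter endpoint need not cost power. That stands: step 4 shows power rising under an unequal loss and staying above 90% under a small common one. A reader might infer that every patient lost to the fibrosis condition pushes the design below 90%. The documents do not support that.

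Four further points limit the claim.

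- **Second component.** The primary outcome also lists fibrosis improvement without worsening of NASH, and the text does not say whether either or both are required. If either suffices, the endpoint may be easier to meet than resolution alone; if both are required, it is harder. One might infer that the planned-for endpoint is simply easier than the real one, but that holds only for the resolution component.
- **Time.** The one-year label is inferred from the matching 85% in the Introduction. The 25% and 69.6% have no time attached, and nothing shows whether resolution at week 96 is lower or higher than at one year.
- **Size of w.** The Introduction calls the fibrosis progression minimal and confined to isolated studies. Its 65.5% with improved fibrosis leaves 34.5% not improved, but that group includes unchanged patients, so it is no useful guide to w.
- **Alpha.** At the 5% level of the analysis section, the normal-approximation power drops below 90% only between w = 10% and 15%.

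Planning from the nearest published endpoint is also common practice. That excuses the choice of inputs; it does not justify presenting the result as power for a different endpoint.

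**Conclusion.** The mismatch of event is plain in the text: the 90% was derived for NASH resolution alone, and the objective and second primary component add a fibrosis condition, read at week 96. On no reading of the primary outcome was the 90% calculated for what the trial will count.

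The size of the effect cannot be established from the documents. The fall from 92% to between 86% and 72% at 1% (98% to between 96% and 88% at 5%) rests on an assumed equal proportional loss of 5 to 15% in both rates. It also keeps the surgery-versus-lifestyle contrast, so it must not be read as the power for ESG versus LSG. Under the illustrative active-arm differences, the comparator mismatch costs far more than the endpoint mismatch. The time-point difference is a further unquantified gap with no known direction.

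**What to change.** In Sample size {14}:

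1. State that the input rates are for NASH resolution with no fibrosis condition, that the 85% matches a one-year result quoted in the Introduction, and that no time point is given for the 25% and 69.6%.
2. Stop presenting 90% as the power for the week-96 primary endpoint.
3. At the fixed n = 30, report power, or the expected confidence-interval width, for the ESG versus LSG difference in NASH resolution without fibrosis worsening at week 96. Use a stated range of assumed rates for these two arms and the alpha that the analysis will apply. Do not enter the 25% lifestyle rate as an arm: a table built on it would show 72 to 92% at the 1% level for a contrast the trial never makes.

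The cost is a few sentences and a small table, with no change to enrolment or conduct. The downside is that the stated power becomes much less favourable.

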#### Trial design {8}

The TESLA-NASH study is a randomized, controlled, open-label, unicentric clinical trial with a sanitary product, designed to evaluate the efficacy of two gastric techniques (endoscopic versus laparoscopic) in the resolution of NASH without worsening liver fibrosis.
Experimental group: ESG + lifestyle modificationsControl group: LSG + lifestyle modifications

A total of 30 eligible participants will be randomly assigned (stratified by the presence or absence of type II diabetes mellitus) to the experimental group or the control group with a 1:1 ratio. The participants will be recruited at the Hospital Marqués de Valdecilla from June 2020 to June 2021.

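### The stated 90% power matches a surgery-versus-lifestyle contrast (85% against 25%) that the trial does not contain, so it does not apply to ESG versus LSG

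*Protocol article*

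**What the plan says.** All of this is in the protocol article.

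- Sample size {14} gives three planning rates for NASH resolution. The first is for surgery in general: "Previous studies have shown a resolution of NASH in the 85% of patients undergoing a bariatric surgery". The other two, for the sleeve operation and for lifestyle change, are given as "69.6% in gastric tubing surgery) and a resolution of 25% in patients with a lifestyle intervention".
- The same section describes the method: "A bilateral ratio comparison test was used for sample size calculation". The settings for that calculation are stated as "with a confidence level of 99%, a statistical power of 90%, and an assumption of 7% loss". The result is 30 patients, 15 per arm. It does not say which two of the three rates were compared.
- Trial design {8} defines the arms: "Experimental group: ESG + lifestyle modificationsControl group: LSG + lifestyle modifications". The Objective under Objectives {7} and Sequence generation {16a} describe the same two arms. None has a lifestyle-only arm.
- The Hypotheses paragraph under Objectives {7} expects ESG to improve liver histology at least as much as the surgical arm. It gives no ESG resolution rate and no margin.
- Statistical methods {20a} compares qualitative variables with a chi-square test and sets a two-sided 0.05 level for all tests.

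**The concern.** A power statement has meaning only for a named difference between the groups being compared. The two rates that appear to lie behind this one are surgery and lifestyle intervention. The trial compares two gastric procedures, each given with lifestyle modification, so 25% describes neither arm. The article also cites a rate for its own control procedure, 69.6%, from which the stated sample size does not follow.

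Readers will take 90% power as the chance of detecting a real ESG-LSG difference. Because the hypothesis is that ESG is at least as good, a non-significant chi-square test is the result most easily read as support for ESG. If real power is low, that result would be likely even when ESG is clearly worse.

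**Working it through.** **Inputs from the article.** Rates 85%, 69.6% and 25%; two-sided alpha 0.01 (99% confidence); power 90%; loss 7%; allocation 1:1. The analysis uses a chi-square test at two-sided 0.05.

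**Step 1: reproduce the stated 30.** The unpooled normal formula per arm is

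n = (z₀.₉₉₅ + z₀.₉₀)² × [p₁(1−p₁) + p₂(1−p₂)] / (p₁−p₂)².

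For 85% against 25%: (2.576 + 1.282)² × (0.1275 + 0.1875) / 0.60² = 13.02, rounded up to 14. Adding 7%: 14 × 1.07 = 14.98, so 15 per arm and 30 in total.

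**Step 2: try the other cited pairs** (same alpha and power, per arm before losses).

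| Pair | Unpooled | Pooled |
|---|---|---|
| 85% vs 25% | 13.02, so 14 | 17.8, so 18 |
| 69.6% vs 25% | 29.9, so 30 | 34.7, so 35 |
| 85% vs 69.6% | 213 | 218 |

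Only 85% against 25% with the unpooled formula leads to 15 per arm.

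**Step 3: can 25% stand for ESG?** No. The hypothesis puts ESG at or above the surgical arm, and both arms receive lifestyle modification on top of a procedure.

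**Step 4: power for the contrast that is randomised.** LSG is set at 69.6%. The article gives no ESG rate, so a range is assumed. Power is the summed binomial probability of every pair of outcomes for which the Pearson chi-square test is significant. The two figures in each cell are for 14 and 15 evaluable patients per arm.

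| Assumed ESG rate | Two-sided 0.05 | Two-sided 0.01 |
|---|---|---|
| 25% | 65%, 70% | 47%, 49% |
| 40% | 32%, 36% | 18%, 19% |
| 50% | 17%, 19% | 7%, 8% |
| 85% | 16%, 18% | 4%, 4% |
| 90% | 26%, 29% | 7%, 8% |
| 100% | 66%, 72% | 23%, 29% |

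**Step 5: what difference is detectable?** At 0.05, 80% power requires ESG at or below about 18% (14 per arm) to 20% (15 per arm), a deficit of about 50 points (69.6 − 20 = 49.6). That is below the 25% cited for lifestyle alone. In the other direction the largest possible gain is 100 − 69.6 = 30.4 points, and even that gives only 66-72%. No ESG rate above 69.6% reaches 80%.

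**Step 6: precision.** The 95% CI half-width is 1.96 × √{[0.696 × 0.304 + p(1−p)]/n}, where p is the ESG rate. With p = 0.696 it is 0.329 (n = 15) or 0.341 (n = 14). With p = 0.50 it is 0.344 or 0.356. So it is about 33 to 36 points.

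**Step 7: sensitivity to the LSG rate.** With LSG at 85% instead, 80% power at 0.05 still needs ESG at or below about 35-38%, and ESG at 50% gives 53-57%.

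**The case against.** The fairest defence is that the article never says 85% and 25% were the inputs. That stands: the pair is inferred by back-calculation, and it works only with the unpooled formula. It does not rescue the power claim, because no other cited pair gives 30 under either formula, and none of the three rates is offered as an ESG rate.

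A second defence is that an article condenses a fuller protocol, which may name an ESG rate. But the point does not rest on an omission. The section prints its rates, alpha, power, loss and result, and the result already follows from a contrast between surgery and lifestyle.

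A third is that the paragraph on the data monitoring committee {21a} presents 30 patients as a source of first results, which is modest. It is, but it does not withdraw the 90% figure.

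A reader might go further and infer any of the following, which the documents do not support:

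- *The arithmetic is wrong.* It reproduces; the fault lies in the contrast chosen.
- *The sample size was really set by feasibility.* No section says so; the article says it was calculated.
- *The trial can detect a 50-point difference either way.* That holds only if ESG is worse.
- *A null result will be presented as coming from a well-powered trial.* That is a prediction about future reporting. The documents show only that the 90% label is there to be misread.

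**Conclusion.** Wrong as written. The stated 90% power is not a property of the ESG-LSG comparison under any ESG rate consistent with the hypothesis: from 69.6% upwards, power at 0.05 never exceeds about 72%, and at plausible gains (85-90%) it is 16-29%. If ESG were truly 20 to 30 points worse (50% or 40%), the trial would detect it about 17-36% of the time. At the 0.01 level used for planning, power is lower still.

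This rests on LSG at the article's sleeve rate, on assumed ESG rates shown as a range, on 14-15 evaluable patients per arm, and on NASH resolution as the outcome, which is the one the planning rates describe. Replacing 69.6% by 85% for LSG changes the numbers but does not restore 90% power for moderate differences. That 85% against 25% were the inputs is an inference, though a firm one. Nothing here requires a larger trial; the claim has to match what 30 patients can show.

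**What to change.** Keep 30 patients and revise the text as follows.

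1. In Sample size {14}, withdraw the 90% power claim for ESG versus LSG, and say which rates and formula produced 30.
2. Use one alpha. Sample size {14} works at 99% confidence and Statistical methods {20a} tests at 0.05. The figures in item 3 assume 0.05 and must be recomputed if 0.01 is kept.
3. State by direction what 15 per arm delivers with LSG at 69.6%: 80% power only if ESG is about 50 points worse (at or below about 18-20%); no ESG rate above 69.6% reaches 80%; a 95% CI half-width of about 33-36 points for ESG between 50% and 69.6%.
4. In the objectives and planned conclusions, describe the comparison as estimation, and state that a non-significant difference will not be read as ESG being equal to LSG.
5. Say that the size was set by feasibility only if that is true.

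The cost is rewording and a less favourable stated figure. No extra patients are needed.
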